## Abstract

**Background:**

This document describes a research protocol for a study designed to estimate the impact of implementing a reminder system for medical providers on the use of isoniazid preventative therapy (IPT) for adults living with HIV in western Kenya. People living with HIV have a 5% to 10% annual risk of developing active tuberculosis (TB) once infected with TB bacilli, compared to a 5% lifetime risk in HIV-negative people with latent TB infection. Moreover, people living with HIV have a 20-fold higher risk of dying from TB. A growing body of literature suggests that IPT reduces overall TB incidence and is therefore of considerable benefit to patients and the larger community. However, in 2009, of the estimated 33 million people living with HIV, only 1.7 million (5%) were screened for TB, and about 85,000 (0.2%) were offered IPT.

**Methods/Design:**

This study will examine the use of clinical decision-support reminders to improve rates of initiation of preventative treatment in a TB/HIV co-morbid population living in a TB endemic area. This will be a pragmatic, parallel-group, cluster-randomized superiority trial with a 1:1 allocation to treatment ratio. For the trial, 20 public medical facilities that use clinical summary sheets generated from an electronic medical records system will participate as clusters. All HIV-positive adult patients who complete an initial encounter at a study cluster and at least one return encounter during the study period will be included in the study cohort. The primary endpoint will be IPT prescription at 3 months post the initial encounter. We will conduct both individual-level and cluster-level analyses. Due to the nature of the intervention, the trial will not be blinded. This study will contribute to the growing evidence base for the use of electronic health interventions in low-resource settings to promote high-quality clinical care, health system optimization and positive patient outcomes.

**Trial registration**
ClinicalTrials.gov NCT01934309, registered 29 August 2013.

## Background

People living with HIV have a 5% to 10% annual risk of developing tuberculosis (TB) disease once infected with TB bacilli, compared to a 5% lifetime risk in HIV-negative people with latent TB infection. Moreover, people living with HIV have a 20-fold higher risk of dying from TB [1]. Active TB disease occurs at any stage of HIV infection and is often the first recognized presentation of the underlying viral infection [2,3]. As such, routinely screening for TB during HIV care creates important opportunities to diagnose and promptly treat active disease, and also to identify those without active TB disease who are eligible for isoniazid preventative therapy (IPT) [4]. A growing body of literature suggests that IPT reduces overall TB incidence and is therefore of considerable benefit to patients and the larger community [5]. For these reasons, the World Health Organization recommends routine, repeated clinical screening for active TB disease among all people living with HIV and the provision of either treatment for active disease or IPT for asymptomatic patients to mitigate the risk of developing active TB [6].

However, in 2009, of the estimated 33 million people living with HIV, only 1.7 million (5%) were screened for TB, and about 85,000 (0.2%) were offered IPT [7]. Greatly improving TB screening, diagnosis and treatment for people living with HIV will require deployment of an effective means of triaging and monitoring this group of patients. While the use of alerts and reminders and associated health informatics solutions to enhance health service delivery is generally well described, this study, to our knowledge, is the first to look at the use of clinical decision-support reminders to directly improve rates of TB screening and initiation of preventative treatment in a TB/HIV co-morbid population.

### Current study

Indiana University, Moi University School of Medicine, the Moi Teaching and Referral Hospital and several other medical school partners have created in western Kenya an innovative and comprehensive response to HIV/AIDS and other health challenges through their support of the Kenyan Ministry of Health. This consortium, the Academic Model Providing Access to Healthcare (AMPATH), promotes and fosters a comprehensive approach to HIV/AIDS control that complements and enhances the existing Kenyan Ministry of Health infrastructure. This initiative supported by the United States Agency for International Development (USAID) strengthens health systems. It addresses food and income security needs, delivers and monitors antiretroviral treatment, and fosters prevention of HIV transmission through community-based health education and prevention of maternal-to-child transmission. Importantly, AMPATH works with all levels of health providers, from the highest levels of government to community health volunteers (CHVs), to provide effective and culturally appropriate care.

The HIV burden in AMPATH’s catchment is large (greater than 15% in some areas). There is a corresponding large clinical enterprise in support of HIV care, which collectively manages approximately 40,000 HIV patient visits per month. Additionally, TB risks to this population are substantial. Nationally, prevalence and incidence rates of TB were estimated to be 299 and 272, respectively, per 100,000 in 2012 [8]. Within the AMPATH network, approximately 45% of patients with active TB have HIV co-infection.

#### Objective

The overall research objective is to evaluate the impact of implementing a reminder system for medical providers (i.e., nurses, clinical officers, medical officers and consultants) to improve TB case-finding and the use of IPT for adults living with HIV in western Kenya. Our main research question is as follows:
Does providing medical personnel with patient-specific reminders regarding TB that are generated from a patient’s electronic medical record and based on clinical algorithms for screening significantly increase IPT prescription rates and decrease the time from initial encounter to IPT initiation?

This study is designed to contribute to the growing evidence base for the use of electronic health (eHealth) interventions to promote high-quality clinical care, health system optimization, and positive patient outcomes. Because this intervention is based on an open-source electronic medical record (EMR) system created specifically for low-resource settings, it is reasonable to conclude that positive results could be replicated in other locations that invest in the basic infrastructure needed to support this system.

## Methods/Design

### Intervention

The intervention to be studied involves providing clinic-based medical care providers (e.g., physicians, nurses and clinical support staff) with patient-specific clinical reminders regarding TB that are generated from a patient’s EMR and based on accepted clinical algorithms for TB screening and treatment.

#### Electronic medical records

The back end of AMPATH’s existing clinical decision-support system (CDSS) is an EMR system that is capable of tracking millions of patient encounters. The AMPATH Medical Record System (AMRS) is one of the world’s largest implementations of the Open Medical Records System (OpenMRS) [9]. AMRS includes more than 100 million clinical observations from more than 300,000 patients. The system tracks data on test results, patient history, physical exam findings, treatment plans, adherence and related information from clinical encounters.

AMRS is optimized for rural western Kenya. Medical personnel complete paper encounter forms at every patient visit, and centralized teams of data clerks enter the data into AMRS [10]. Pilot studies are underway to guide the transition to electronic data entry at the point of care, but currently records are digitized centrally. This makes it feasible to extend the coverage of the EMR system to include the most remote facilities that do not have reliable power or access to computers or tablets.

#### Clinical decision support

Prior to a patient’s next scheduled visit, clinic personnel print a paper clinical summary sheet that gives vital details and patient-specific care suggestions, which are automatically generated by the system based on a defined set of rules [11]. This summary sheet promotes effective task shifting as it helps providers with modest levels of training to provide high-quality standardized care [12].

There are currently more than 60 possible clinical care reminders that could be triggered and printed on a patient’s summary sheet, but there is only enough space to display a few of the most relevant reminders for each patient. The only TB-related reminder currently used in the system is a reminder about the need to conduct and report the results of a chest radiograph (CXR), which is usually performed at the initial encounter to rule out active pulmonary infection.

#### Tuberculosis clinical care reminders

As part of this study, we created a new set of reminders for TB prevention and treatment based on accepted clinical algorithms [13]. These reminders are designed to prompt medical providers to complete TB screening, consider initiating anti-TB treatment or IPT, and monitor adherence to treatment based on clinical data that exist in AMRS.

For example, if a patient does not have a history of TB or IPT, the results of a physical examination and patient-reported symptoms are not suggestive of active TB, and CXR results are normal, the paper summary sheet printed for the patient’s next visit will include the following reminder:
Test results do NOT suggest active TB. If patient still does NOT report TB symptoms, consider initiating IPT. IPT is effective and could save [his/her] life.

### Study design

#### Type of study

This will be a pragmatic, parallel-group, cluster-randomized superiority trial involving 20 public medical facilities in the AMPATH network in western Kenya.

#### Treatment group specification and assignment

Clusters will be sorted into four strata and randomly assigned to the treatment or control group with an allocation ratio of 1:1. The two stratifying variables will be average monthly patient volume and the percentage of initial patient encounters in 2013 with CXR results recorded in AMRS. Stratifying on cluster size is advantageous when cluster sizes vary in the population and when cluster size might be correlated with the endpoint of interest [14]. Stratifying on the availability of CXR results in AMRS will potentially reduce the imbalance on a cluster-level covariate that we expect will be related to isoniazid (INH) prescribing behavior.

AMPATH clinical protocols advise that all patients should have a normal CXR that is no more than 6 months old before medical providers prescribe IPT (assuming no other contraindications). However, in 2013, fewer than a third of initial encounters with HIV-positive adults had CXR results recorded in AMRS. When results are missing from AMRS, CDSS will print a general reminder about ordering a CXR. At best, a general reminder that prints for most patients will potentially lead to reminder fatigue. At worst (when CXR results exist and are known to the provider), the prompt to order a CXR is a false positive; in these cases, the summary sheet should contain a more specific reminder about considering anti-TB treatment or IPT based on the CXR result and patient symptoms, not a reminder to order a CXR. We expect the general reminder to order a CXR, particularly where the printing of this reminder is a false positive, to be less impactful on INH prescribing behavior. We also expect these messages to be more common at facilities that are less successful in entering CXR results into AMRS. Therefore, we will stratify randomization on baseline facility-level availability of CXR results in AMRS.

Both stratifying variables will be dichotomized (volume greater than 1,000 patients per month and percentage of results in AMRS greater than 23%) to create four possible strata: low volume/low results; low volume/high results; high volume/low results; high volume/high results.

Clinical summary sheets for patients receiving care at treatment clusters will include the new TB care reminders (as needed) *plus* the full set of existing reminders, whereas summary sheets printed at control clusters will only include the existing set of reminders (i.e., no new TB care reminders).

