The final eligibility criterion is that a patient must attend at least one additional appointment within 90 days of her initial encounter so that her provider has the opportunity to be exposed to the CDSS reminders on the summary sheet. Since a patient’s initial encounter is her first contact with AMPATH at the facility level, there is no summary sheet available during a patient’s initial encounter.

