##### Cluster-level summaries

To determine if there is a statistically significant difference in the proportion of INH prescriptions among IPT-eligible patients between treatment and control clusters, we will use an unpaired *t*-test. We will also estimate the relative risk of INH prescription and associated 95% confidence intervals. We will use Kaplan–Meier methods to calculate the proportion of eligible patients receiving INH prescriptions within 3 months of their initial encounters. To test the null hypothesis that there is no difference between the survival curves, we will use the log rank test.

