##### Individual-level regression analysis

In addition to the analyses based on cluster-level summaries, we will also use regression models with individual-level data that account for between-cluster variation. Specifically, we will evaluate the reliability of logistic regression random effects models and generalized estimating-equation approaches to model our binary outcome. We will use Cox regression with random effects to model the time to INH prescription. Individual-level covariates will be limited to data collected reliably in AMRS, such as age, gender and CD4 count.

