#### Statistical design considerations

This will be a pragmatic, parallel-group, cluster-randomized superiority trial with a 1:1 allocation to treatment ratio from within four strata. Assuming a desired power of 0.80, alpha of 0.05, 20 clusters equally allocated to treatment and control, 50 patients per cluster, a between-cluster coefficient of variation of 0.25 and a baseline INH prescription rate of 15%, we will be able to detect a minimum shift of almost 8 percentage points in the INH prescription rate, from 15% to almost 23% using a one-tailed test^e^.

Based on a recent retrospective review of AMRS data, we believe that the current rate of INH prescription is between 5% and 25%. Historically, this rate was higher at nearly 40%. No matter where the true baseline rate is in this range, our minimum detectable effect is not projected to rise above 8 percentage points, if everything else is held constant.

The between-cluster coefficient of variation is also important in this calculation. Without cluster-level baseline data on the INH prescription rate, we have to estimate. This variation is often less than 0.25 and rarely exceeds 0.50 [15]. In the previous calculations, we set the between-cluster variation to be 0.25 and scaled it down by 0.75 to account for the benefits of stratification. If the between-cluster variation is really at the high end of this range before scaling (0.50), then the minimum detectable effect climbs to almost 12 percentage points. If we further assume that it is only possible to observe half as many patients per cluster (25), the minimum detectable effect increases to 14 percentage points.

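### Allocation is stratified on 2013 CXR availability and the power calculation takes credit for it, but no stated analysis uses the strata or the covariate

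*Protocol article*

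**What the plan says.** Treatment group specification and assignment defines four strata from monthly patient volume and the 2013 percentage of initial encounters with a CXR result in AMRS. It describes CXR availability as "a cluster-level covariate that we expect will be related to isoniazid (INH) prescribing behavior". Both variables are dichotomised, CXR availability at "percentage of results in AMRS greater than 23" per cent.

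The analysis sections do not return to either variable:

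- Cluster-level summaries: for the difference in proportions "between treatment and control clusters, we will use an unpaired" t-test. No stratum or covariate term is mentioned.
- Individual-level regression analysis: "Individual-level covariates will be limited to data collected reliably in AMRS, such as age, gender and CD4 count". No cluster-level term is named.
- Subset analyses: age, gender, CD4 count and number of reminders, but not CXR availability.

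Statistical design considerations sets power at 0.80 and alpha at 0.05, with 10 clusters in each arm and 50 patients in each cluster. Its other inputs are "a between-cluster coefficient of variation of 0.25 and a baseline INH prescription rate of 15" per cent. It reports the detectable shift as running "from 15% to almost 23% using a one-tailed test". It then explains that the CV was multiplied by 0.75 for stratification, and endnote e cites a formula for stratified cluster trials.

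**The concern.** The sample size assumes that stratification removes part of the between-cluster variance. An unpaired t-test does not take that gain. Stratified allocation balances the strata across arms, so between-stratum variance largely drops out of the estimated difference, but it remains in the standard error that the test uses. The test is then conservative and loses power.

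A cut at 23% also discards information. Facilities on the same side of it can differ widely in CXR availability. If prescribing follows availability, that variation stays in both the estimate and its standard error.

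With only 20 clusters, power is scarce. The covariate that could recover some of it was computed before launch in order to randomise, yet it plays no part in the stated analysis.

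**Working it through.** **Reproducing the plan's figures.** Inputs from Statistical design considerations: 10 clusters per arm, m = 50, p0 = 0.15, one-sided alpha 0.05, power 0.80, CV k = 0.25 multiplied by 0.75 to give 0.1875. The cited equation is not printed in the article. The form below, with a leading term of 1, reproduces all three stated detectable effects:

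c = 1 + (z_alpha + z_beta)² × [p0(1−p0)/m + p1(1−p1)/m + k²(p0² + p1²)] / (p1 − p0)²

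With (1.645 + 0.842)² = 6.18 and p1 = 0.2272:

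- within-cluster part: 0.1275/50 + 0.1756/50 = 0.00606
- between-cluster part, scaled: 0.1875² × (0.0225 + 0.0516) = 0.00261
- c = 1 + 6.18 × 0.00867 / 0.0772² = 10

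**Size of the credit.** Multiplying the CV by 0.75 assumes that the two stratifiers together remove 1 − 0.75² = 43.75% of between-cluster variance. Unscaled, the between-cluster part is 0.25² × 0.0741 = 0.00463 and the total is 0.01069. The credit is therefore (0.00463 − 0.00261)/0.01069 = 19% of total variance. The whole between-cluster part is 43% of the total. The other 57% is sampling variance within clusters, which a facility-level covariate cannot remove.

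| CV before scaling, m | Detectable effect as stated | Reproduced with 0.75 | Without 0.75 | Formula power at the reproduced effect, without 0.75 |
|---|---|---|---|---|
| 0.25, 50 | almost 8 points | 7.7 | 8.7 | 72% |
| 0.50, 50 | almost 12 points | 11.6 | 15.7 | 64% |
| 0.50, 25 | 14 points | 13.9 | 17.9 | 67% |

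**Unpaired against stratum-adjusted test, by simulation** (20 clusters, 50 patients each, assumed stratum sizes 4/6/4/6, effects 7.7 and 11.6 points):

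| Strata share of between-cluster variance | CV 0.25: unpaired v adjusted | CV 0.50: unpaired v adjusted |
|---|---|---|
| 0% | 73% v 73% | 67% v 67% |
| 20% | 74% v 76% | 69% v 73% |
| 43.75% | 76% v 81% | 70% v 82% |

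In the last row at CV 0.25, the true standard error of the difference is 0.0291, but the unpaired test reports 0.0324 on average. Its one-sided type I error is 3.4% (2.3% at CV 0.50) against the nominal 5%.

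**Unpaired test against adjustment for the continuous 2013 percentage, by simulation:**

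| CXR share of between-cluster variance | CV | Unadjusted v adjusted power |
|---|---|---|
| 0% | 0.25 | 74% v 72% |
| 20% | 0.25 | 75% v 76% |
| 44% | 0.25 | 73% v 78% |
| 70% | 0.25 | 75% v 85% |
| 44% | 0.50 | 70% v 80% |

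Type I error was about 5 to 6% adjusted and 3 to 5% unadjusted. The CXR shares are assumptions. The article's only related figure is the 0.75 factor, which covers volume and CXR jointly and is itself assumed.

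**The case against.** The strongest reply is that nothing here is an error. An unadjusted t-test after stratified randomisation is valid, and chance imbalance within strata is ordinary sampling variation. The covariate list is open, and a full list is usually left to the analysis plan. Much of this stands: the comparison is not biased, and the silence of the individual-level section alone would not be a finding. But the cluster-level test is fixed in the text, and the power calculation takes a gain which that test does not collect. That is a mismatch between two stated parts of the plan. The open list is also confined to individual-level data.

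A second reply is that the CXR argument is partly about which reminder prints. The specific IPT reminder exists only in treatment clusters, so CXR availability may modify the effect more than it predicts prescribing. That is a fair reason to doubt the strength of the link. However, the article also says that network protocols in general advise a normal CXR before IPT, which applies in both arms.

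A reader might infer that a large, removable part of the variance is being left in. The documents do not support this. They give no correlation, no spread of CXR availability across facilities and no prescribing rates by CXR status. CXR is also not the only predictor named: cluster size, age, sex and CD4 count appear too.

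A reader might also want to adjust for a patient-level indicator of a CXR result from the initial encounter, since "there is no summary sheet available during" that visit. The indicator is nevertheless recorded after randomisation. It depends on later data entry and form correction, and providers in treatment clusters will have seen the new reminders for other patients. The Patients section names screening and diagnosis as a target of the intervention, so adjusting for the indicator could remove part of the effect.

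**Conclusion.** The point holds as a mismatch between design and analysis. The strata and the 2013 CXR percentage are used in allocation, stratification is credited in the power calculation, and neither variable appears in a stated analysis. The consequence is a conservative, less powerful cluster-level test; the documents do not support a claim of bias or of an invalid test.

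The size is conditional. If CXR availability explains 0 to 44% of between-cluster variance, adjustment gains about 0 to 5 power points at CV 0.25 and 0 to 10 at CV 0.50, and more if it explains more. With no link, one or two points are lost. The unscaled formula figures in the first table somewhat overstate the loss when the strata do matter, because balanced allocation already reduces the true sampling error: the simulated power of the unpaired test is then 76% and 70%, against 72% and 64% by formula. The change is worth making because the covariate already exists and predates launch.

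**What to change.** In Cluster-level summaries, replace the unpaired t-test with a linear regression of the 20 cluster prescription proportions on arm, the continuous 2013 CXR percentage and the volume stratum. Add the same pre-launch terms to the logistic, estimating-equation and Cox models in Individual-level regression analysis. Report the unadjusted result beside the adjusted one. Use a patient-level CXR indicator at most in a sensitivity analysis.

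The cost is a sentence or two of text and one or two of the 18 degrees of freedom, with no new data collection: the 2013 percentage was needed for randomisation and predates the April 2014 launch.

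If the unpaired t-test is kept instead, remove the 0.75 factor and restate the detectable effects as about 8.7, 15.7 and 17.9 percentage points.
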